### Statistical Analysis

2.8

All statistical analyses will be performed using SPSS (Statistical Package for the Social Sciences), version 25 (IBM Corp., Armonk, NY, USA). Descriptive statistics will be presented as frequencies, percentages, means, and standard deviations, as appropriate. For between‐group comparisons of baseline characteristics, independent‐samples *t* tests will be used for continuous variables, and Pearson's Chi‐square (*χ*
^2^) tests will be used for categorical variables. Changes in outcome measures across the three assessment time points will be evaluated using repeated‐measures analysis of variance, with group, time, and group × time interaction effects examined to assess differences in trajectories between the intervention groups. Where appropriate, post hoc comparisons will be performed with adjustment for multiple comparisons. ESs will be estimated using partial eta squared (ηp^2^) for the repeated‐measures analyses and Cohen's d for pairwise comparisons, with Cohen's d values of 0.20, 0.50, and 0.80 interpreted as small, moderate, and large effects, respectively. Between‐group mean differences will be reported with corresponding 95% confidence intervals (CIs) to enhance the precision and clinical interpretability of the estimates. All analyses will follow the intention‐to‐treat principle, including all randomized participants in the analysis according to their assigned groups. Missing data will be addressed using multiple imputation under a missing‐at‐random assumption. A two‐sided *p*‐value of < 0.05 will be considered statistically significant.

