### Outcome Measurements

2.6

Outcome measures included sociodemographic information such as gender, body mass index (BMI), duration and severity of symptoms, radiological findings, comorbidities assessed using the Charlson Comorbidity Index (CCI), history of falls in the past year, physical activity, and other factors relevant to KOA. Primary outcomes focus on pain and functional status, while secondary outcomes include lower‐limb‐specific muscle strength, knee ROM, and functional mobility. Questionnaires were initially developed in English and then translated and back‐translated into Bengali by a bilingual researcher to ensure accuracy and consistency. All outcomes are planned to be assessed at baseline, post‐intervention (8 weeks), and follow‐up (6 months) using questionnaires and clinical examinations, with measurements conducted by trained, blinded assessors.

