### Sample Size Calculation

2.7

G*Power, version 3.1.9.7 (University of Kiel, Kiel, Germany), was used to determine the required sample size for this study. The calculation indicates that a total of 68 participants are required, with an effect size (ES) of 0.61 for the functional outcomes, an *α* level of 0.05, and a power of 0.80 [29]. Therefore, each group requires 34 participants. After accounting for a 15% dropout rate, the number of participants in each group is increased to 40, resulting in a final estimated total of 80 participants.

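### Baseline t and chi-square tests say little about comparability and may be misread; the collected prognostic variables would serve better as prespecified covariates

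*Protocol article*

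**What the plan says.** Protocol article, section 2.8 (Statistical Analysis), names a significance test for "comparisons of baseline characteristics" between the arms: independent-samples t "tests will be used for continuous variables" and Pearson chi-square "tests will be used for categorical variables". The only threshold in the section is its general one, a two-sided p-"value of < 0.05 will be considered statistically significant". Descriptive statistics are also planned. The section does not say what follows from a significant or a non-significant baseline result.

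Section 2.6 (Outcome Measurements) lists the characteristics collected. Besides gender and BMI these include "duration and severity of symptoms, radiological findings, comorbidities assessed using the Charlson Comorbidity Index (CCI"), falls in the past year and physical activity. The six outcomes are also measured at baseline.

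The outcome model in section 2.8 is a repeated-measures ANOVA over three time points with group, time and group × time. No baseline covariate is named. Section 2.4 describes 1:1 allocation by sealed envelopes and mentions no stratification, while section 2.3 admits KL grades II and III.

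**The concern.** A significance test asks whether a difference is larger than chance would produce. Where allocation is random, chance is already known to be the source of baseline differences, so the test answers a question nobody needs to ask. The useful question is whether an observed imbalance is large enough, in a variable prognostic enough, to matter for the outcome comparison. A p-value at 40 per arm does not answer that.

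Two misreadings become easy. One significant result among many may be taken as failed randomisation, and a table without significant results may be taken as proof of comparable groups. A third risk is that covariates are added after the p-values are seen, which the plan does not rule out. Meanwhile the variables that could sharpen the outcome comparison are collected but have no stated place in the model.

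**Working it through.** **Inputs.** Section 2.7 gives 34 per arm before dropout and 40 per arm after 15% dropout: 34 / 0.85 = 40, which reproduces. The plan gives no figure for the baseline tests themselves, so there is none to reproduce. The threshold is two-sided 0.05 (section 2.8) and the planned effect is 0.61 (section 2.7). The number of baseline tests is not stated. Section 2.6 names about 8 characteristics and there are 6 baseline outcomes, so about 14; I use a range of 8 to 20.

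**1. Chance of at least one significant baseline test.** With k independent tests, each with a 5% false-positive rate, P = 1 − 0.95^k.

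| k | P(at least one p < 0.05) |
|---|---|
| 8 | 34% |
| 10 | 40% |
| 14 | 51% |
| 20 | 64% |

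Several of these variables overlap (VAS and WOMAC both measure pain, for example), so the true figures are somewhat lower.

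**2. Largest observed imbalance that passes.** The standard error of a standardised mean difference is √(2/40) = 0.224. The two-sided 5% critical value of t on 78 degrees of freedom is about 1.99. The threshold is 1.99 × 0.224 ≈ 0.445 SD. Every observed imbalance smaller than that is reported as non-significant.

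**3. How often a sizeable imbalance arises.** P(|d| > 0.3) = P(|Z| > 0.3/0.224) = P(|Z| > 1.34) ≈ 0.18 for any one variable. The test flags 5% of all allocations, and all of those lie beyond 0.445 SD. Of the allocations with an imbalance above 0.3 SD, about 0.05/0.18 = 28% are flagged and about 72% are not.

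**4. What such an imbalance does to the estimate.** In an unadjusted comparison at one time point, a factor with imbalance d and correlation r with the outcome moves the estimate by r × d. The documents give no r; I assume 0.4 to 0.6.

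- r = 0.4: 0.4 × 0.3 = 0.12 SD, and 0.12/0.61 = 20% of the planned effect.
- r = 0.6: 0.6 × 0.3 = 0.18 SD, and 0.18/0.61 = 30% of the planned effect.

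**5. The same imbalance in the group × time contrast.** Here the baseline outcome is subtracted. With equal outcome SDs the shift is (r at follow-up − r at baseline) × d. It is zero if the two correlations are equal and otherwise depends on the factor's relation to change. So the figures in step 4 partly cancel in the interaction and apply in full only to between-group differences at a single time point. If the imbalance is in the outcome's own baseline value, a change contrast is still exposed to regression to the mean.

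**The case against.** The strongest reply is that these tests do no direct harm. Section 2.8 attaches no adjustment, exclusion or conclusion to them, and it plans descriptive statistics as well. Sample size, the outcome model and the type I error on the outcomes are all unchanged by them. This stands, and it sets the severity.

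Four stronger readings are tempting, and the documents do not support them.

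- **That comparability will be misread, or is decided by these tests.** The protocol says only that the tests will be done. How they are read is a prediction; the supportable statement is that they may be misread.
- **That an imbalance of 0.3 SD biases the result.** Over repeated randomisations, chance imbalance adds variance, which the confidence interval already reflects. The 0.12 to 0.18 SD is an error in one realised allocation, under an assumed correlation, in an unadjusted single-time-point comparison.
- **That the test detects a 0.3 SD imbalance 26% of the time.** That figure is power against a true underlying difference, which randomisation rules out. An observed 0.3 SD imbalance at 40 per arm is never significant.
- **That leaving out covariates is itself an error.** Covariate choice is commonly left to a statistical analysis plan, which is not shown here. The case rests on the tests the article does prescribe and on the model it does state.

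One further qualification holds. Section 2.4 assigns different assessors to each group. If that applied at baseline, differences in assessed measures could reflect the assessor as well as chance, and a significance test could not tell the two apart.

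**Conclusion.** The concern holds as a minor point. The planned tests are uninformative about balance: they would flag something in 34% to 64% of properly randomised trials (8 to 20 independent tests assumed) and would pass any observed imbalance below about 0.445 SD. They leave room for misreading and for covariates chosen after the p-values are seen.

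Deleting them alone would change no outcome result. The practical gain comes from naming covariates in advance, which should improve precision over the stated unadjusted model and closes off data-driven adjustment. The 20% to 30% figure illustrates what one chance imbalance could do in a single-time-point comparison; it rests on the assumed correlation of 0.4 to 0.6 and is not an estimate of bias in the planned interaction test.

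**What to change.** In section 2.8, or in the statistical analysis plan if one exists:

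- Remove the baseline t and chi-square tests. Present baseline values by arm as means (SD) or counts, without p-values.
- Before unblinding, specify that the between-group outcome analysis adjusts for the baseline value of the outcome, KL grade (II/III) and at most one other collected prognostic factor, such as symptom duration. State that these stay in whatever balance is observed. An outcome's baseline value cannot be both a covariate and a time level in one model, so this adjustment belongs in the comparison of the 8-week and 6-month values.

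The choice of KL grade and symptom duration is a suggestion from among the variables already collected; what matters is fixing the list in advance.

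The cost is about two sentences and 1 to 3 degrees of freedom out of about 78 (80 participants less 2 group means). No new data or participants are needed, and N stays at 80. The article reports no outcome data as yet and keeps the statistician blinded until the analysis is complete, so the change can still be made in time.

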### Study Design

2.1

This study is a multicenter, assessor‐blinded, RCT comparing the effects of KT with NCE (experimental group) versus sham KT with NCE (control group) in a 1:1 ratio among 80 KOA patients in Bangladesh. Each group's intervention lasts 8 weeks, with three sessions per week, followed by a 6‐month follow‐up. Primary and secondary outcomes were planned to be measured at baseline, post‐intervention, and follow‐up. The study obtained ethical approval and was registered in the Clinical Trial Registry. To ensure transparency, the study adhered to the 2013 SPIRIT (Standard Protocol Items: Recommendations for Interventional Trials) guidelines (Table 1). Additionally, the CONSORT (Consolidated Standards of Reporting Trials) statement guidelines will be utilized to ensure transparent reporting of the findings (Figure 1).

**Table 1 hsr273125-tbl-0001:** SPIRIT guidelines.

Timepoint	Enrollment	Allocation		Post‐allocation	
	−T_1_	T_0_	T_1_	T_2_	T_3_
Enrollment					
Eligibility screening	X				
Informed consent		X			
Demographic and clinical assessment			X		
Group allocation		X			
Intervention					
Experimental group			X	X	
Control group			X	X	
Assessment					
VAS			X	X	X
PPT			X	X	X
WOMAC			X	X	X
Muscle strength			X	X	X
ROM			X	X	X
TUG			X	X	X

*Note:* −T_1_ = pre‐study enrollment; T_0_ = group allocation; T_1_ = baseline before intervention; T_2_ = measurement after 8 weeks; T_3_ = measurement after 6 months.

Abbreviations: PPT, pressure pain threshold; ROM, range of motion; TUG, Timed UP and Go test; VAS, visual analog scale; WOMAC, Western Ontario and McMaster University Osteoarthritis Index.

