### Participants and Recruitment

2.2

Participants meeting the eligibility criteria were recruited from the four participating branches of the Centre for the Rehabilitation of the Paralysed (CRP), Bangladesh, through routine physiotherapy services, clinical records, and referrals. A trained research assistant who was not involved in intervention delivery or outcome assessment conducted the initial screening using a standardized eligibility checklist. Recruitment commenced in September 2025 and is expected to continue through December 2026, including follow‐up. Eligible individuals received detailed information about the study procedures, potential benefits and risks, confidentiality, and their right to withdraw at any time without affecting their usual care. Written informed consent was obtained before enrollment and any study‐specific assessment. Recruitment procedures were designed to ensure equitable and impartial participant selection across the participating sites.

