### Randomization and Blinding

2.4

Participants were randomly assigned in a 1:1 ratio to receive KT with NCE or sham KT with NCE. Randomization was carried out using sequentially numbered, opaque, sealed envelopes prepared by an independent researcher who was not involved in recruitment or assessment. The allocation was revealed only after the baseline assessment. Baseline, post‐intervention, and follow‐up assessments are conducted by blinded outcome assessors, with different assessors assigned to each group. Intervention delivery and KT application are performed by separate therapists who are not involved in outcome assessments. The statistician will remain blinded to group allocation until the analysis is complete. Due to the nature of the intervention, participant and therapist blinding was not possible. The success of blinding will be evaluated after the study concludes.

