The study findings could significantly benefit KOA management practice by endorsing a safe, cost‐effective, and easily implementable intervention that requires neither sophisticated equipment nor extensive financial investment. The strengths of this study include its multicenter design, assessor blinding, adequate sample size, standardized intervention protocol, and long‐term follow‐up. These methodological features enhance the internal validity and reliability of the results. However, some limitations should be considered. The study is being conducted in a Bangladeshi population, which may limit the generalizability of the findings to other populations and healthcare settings. Variations in exercise adherence and follow‐up participation may influence the study outcomes. Although adverse events are expected to be minimal, some participants may experience discomfort or delayed‐onset muscle soreness, which may affect their adherence to or engagement with the intervention. Furthermore, as both groups are receiving the same NCE program, the study is primarily designed to determine the additional effect of KT rather than the independent effects of KT or NCE alone. Future research should investigate the long‐term sustainability, cost‐effectiveness, and cross‐cultural applicability of KT combined with NCE or other exercise interventions, while incorporating advanced radiological imaging to assess structural changes across different stages of KOA.

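### The stated model has no term for branch or baseline, so the 8-week and 6-month between-group differences leave that variation in the error and chance imbalance uncorrected

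*Protocol article*

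**What the plan says.** Section 2.1 of the protocol article states "This study is a multicenter, assessor‐blinded, RCT", with 80 patients allocated 1:1. Section 2.2 says they are "recruited from the four participating branches of the Centre for the Rehabilitation of the Paralysed". The Discussion counts this in the trial's favour: "The strengths of this study include its multicenter design".

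On allocation, section 2.4 says "Participants were randomly assigned in a 1:1 ratio to receive KT with NCE or sham KT with NCE", using "sequentially numbered, opaque, sealed envelopes prepared by an independent researcher". Stratification or blocking by branch is not mentioned.

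On analysis, section 2.8 says "Changes in outcome measures across the three assessment time points will be evaluated using" repeated-measures ANOVA (baseline, 8 weeks and 6 months), "with group, time, and group × time interaction effects examined to assess differences in trajectories between the intervention groups". It names no branch term and no covariate; baseline enters as one of the three levels of the response. The same section promises between-group mean differences with 95% confidence intervals, and Cohen's d for pairwise comparisons. Section 3 says superiority over sham will be judged at 8 weeks and at 6 months.

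**The concern.** Branch and baseline value are known for every participant before treatment starts. Baseline pain or function usually predicts later pain or function. Branch may do so as well: recruitment runs through each branch's routine services and referrals, and several outcomes depend on the examiner (pressure pain threshold, goniometry, sphygmomanometer strength). As described, branch is used neither in the allocation nor in the model.

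Two things are at stake, both in the differences at a single time point. The first is precision: variation that could be removed stays in the error and widens the intervals. The second is chance imbalance: if the arms fall unevenly over branches or differ at baseline, the observed difference carries that imbalance and nothing in the stated model takes it out.

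**Working it through.** **Inputs.** From section 2.7: d = 0.61, α = 0.05, power 0.80, 34 evaluable and 40 randomised per arm, 15% dropout. From section 2.8: two-sided test. From section 2.2: four branches. The article gives no branch variance, branch sizes or baseline correlation, so these are assumptions shown as ranges.

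**The plan's own figure.** A two-sample comparison with d = 0.61 and power 0.80 needs 34 per arm with a one-sided 0.05 test (power 0.801). The inflation 34 / 0.85 = 40 reproduces 80 in total. With a two-sided test, 34 per arm gives power 0.698 and 40 per arm gives 0.769. The one-sided/two-sided discrepancy is a separate matter; these two-sided values are only the starting point here.

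**1. Branch term alone, one time point.** Let ρ be the share of outcome variance explained by branch. With branch in the model, the standardised effect becomes 0.61 / √(1 − ρ) and the error degrees of freedom fall by 3, to 2n − 5. Power comes from the noncentral t with noncentrality effect × √(n/2).

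| ρ (assumed) | Effect | Power, 34 per arm | Power, 40 per arm |
|---|---|---|---|
| no branch term | 0.610 | 0.698 | 0.769 |
| 0% | 0.610 | 0.697 | 0.768 |
| 1% | 0.613 | 0.702 | 0.772 |
| 5% | 0.626 | 0.719 | 0.789 |
| 10% | 0.643 | 0.742 | 0.810 |
| 15% | 0.662 | 0.766 | 0.832 |

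**2. Chance imbalance.** Assume four branches of 20 and a 40:40 allocation not balanced by branch. At least one branch is split 13:7 or worse in about 52% of allocations (200,000 simulated). To turn this into a shift of the group difference, let x be the number of a branch's 20 participants who receive KT.
- Var(x) = 40 × ¼ × ¾ × 40/79 = 3.80.
- The branch's weight in the difference is (2x − 20)/40, with variance 4 × 3.80/1600 = 0.0095.
- Over four branches the shift has variance 4 × 0.0095 × ρ = 0.038ρ, so its SD is about 0.195√ρ.
- This is 0.02, 0.04 and 0.06 outcome SDs at ρ = 1%, 5% and 10%, against a standard error of √(2/40) = 0.22 for the difference itself.

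**3. The group × time test.** A branch effect that is constant over time drops out of every within-participant difference. In one simulated data set of 80, adding a constant branch effect left the group × time F at 0.8797 and moved the group main-effect F from 0.0122 to 0.0001. A branch effect that varied over time moved the group × time F from 0.8797 to 0.8651.

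**4. Baseline value.** Assume a correlation r = 0.5 between baseline and follow-up. The change score has variance 2(1 − 0.5) = 1, the same as the follow-up value, so analysing change gains nothing over the raw comparison. With baseline as a covariate, the effect becomes 0.61 / √(1 − 0.25) = 0.704. Power is then 0.82 instead of 0.70 at 34 per arm, and about 0.87 instead of 0.77 at 40 per arm.

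**5. Branch on top of baseline.** Suppose the branch effect is stable, so that it is shared by baseline and follow-up. The within-branch correlation is (0.5 − ρ)/(1 − ρ), and the residual variance is (1 − ρ) × (1 − that correlation²). With 62 degrees of freedom at 34 per arm:
- ρ = 5%: correlation 0.45/0.95 = 0.474, residual 0.737, power 0.822.
- ρ = 10%: correlation 0.40/0.90 = 0.444, residual 0.722, power 0.830.

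Against 0.816 with baseline alone, branch adds about 1 point, compared with 2 to 4 points in step 1.

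**The case against.** The strongest reply is that centre and covariate adjustment is commonly left to a statistical analysis plan, which is not shown, and that section 2.8 does not exclude such terms. That would answer a complaint about missing detail. Here the article states the model's effects, and the point is that this stated model can be improved; a later plan that added branch would be changing what is published.

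Four stronger readings are tempting and should not be made.

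- A reader might infer that each branch has its own therapists and assessors. The article does not say so. Section 2.4 describes assessors by group and says only that therapists are separate from them. Section 2.5 adds common training, manuals and checklists. A branch effect is plausible, but none is documented.
- A reader might infer that branch variation weakens every test. Step 3 shows that stable branch differences, and any imbalance in them, cancel in group × time.
- A reader might call the chance imbalance bias. Under individual randomisation it is random error, already reflected in the standard error, and omitting branch does not inflate type I error. What is lost is precision, and correction of the particular imbalance that occurs.
- A reader might take the two-sided power of about 0.70 as harm done by omitting branch. It comes from the sample-size calculation.

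It is also fair to say that baseline cannot simply be added to the stated ANOVA, where it is already a response level, and that a branch main effect would leave group × time unchanged. Both objections stand, and the fix is framed accordingly.

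**Conclusion.** The point holds in a limited form, as a worthwhile improvement rather than an error that invalidates the analysis. It concerns the group main effect and the 8-week and 6-month between-group differences, with their effect sizes and intervals.

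The gain from branch alone ranges from nothing (a loss of 0.001 in power at a 0% share) to about 2 to 4 points at 5% to 10%. The branch share is an assumption throughout, and the imbalance figures also assume four equal branches. The larger gain comes from the baseline value, about 10 points or more at an assumed correlation of 0.5, after which branch adds little. All power figures are for a two-group comparison at one time point, not for the repeated-measures interaction.

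**What to change.** Before unblinding, specify that the 8-week and 6-month between-group differences and their 95% confidence intervals are estimated from a model of the post-baseline values. This can be an ANCOVA at each time point or a mixed model over both, with the baseline value of the outcome as covariate and branch as a fixed factor. Apply it to the primary and secondary outcomes. State also whether the envelopes were prepared by branch.

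The cost is 4 degrees of freedom (3 for branch, 1 for baseline), from 66 to 62 at 34 per arm, and a change from baseline as a repeated level to baseline as a covariate. No new data are needed beyond a record of each participant's branch.

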## Results

3

This study is a protocol for a RCT; therefore, no outcome data have been collected, and results are not yet available. It is anticipated that both KT combined with NCE and sham KT with NCE will improve primary outcomes, including pain intensity, PPT, and functional status. Secondary outcomes are expected to improve lower‐limb muscle strength, knee ROM, and functional mobility. Between‐group analyses will assess whether the addition of KT provides superior clinical and statistical benefits compared with sham KT with NCE at post‐intervention (8 weeks) and follow‐up (6 months). Data on treatment adherence, adverse events, and intervention feasibility will also be reported. Final results will be disseminated through peer‐reviewed journals and scientific conferences.

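### Repeated-measures ANOVA with baseline as an outcome level is valid but usually less efficient than a baseline-adjusted comparison at 8 weeks and 6 months, and its group main effect should not be read as the treatment effect

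*Protocol article*

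**What the plan says.** Section 2.8 of the protocol article analyses the outcomes at all three assessments by repeated-measures ANOVA, "with group, time, and group × time interaction effects examined to assess differences in trajectories between the intervention groups". Table 1 and section 2.6 show that one of the three assessments is the baseline taken before intervention, so baseline is a level of the outcome and not a covariate.

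The same section adds multiplicity-adjusted post hoc comparisons where appropriate, partial eta squared, Cohen's d for pairwise comparisons, and between-group mean differences with 95% CIs. It names no visit for those differences and no baseline adjustment. It also states: "Missing data will be addressed using multiple imputation under a missing‐at‐random assumption".

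The question in section 1.1 concerns differences just after the 8-week programme and at 6 months. Section 3 repeats this: the between-group analyses will assess "whether the addition of KT provides superior clinical and statistical benefits compared with sham KT with NCE" at both times. Neither visit is ranked first.

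**The concern.** None of the three listed model effects estimates the quantity asked for.

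- The time effect is not a treatment comparison.
- The group effect averages the two follow-up visits with a pre-treatment visit at which randomisation makes the expected difference zero.
- The group × time effect is an omnibus test on 2 degrees of freedom. It does not say at which visit the groups differ.

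Baseline is measured on everyone and usually predicts follow-up. Using it as a covariate normally narrows the confidence interval for the treatment difference. At stake are some power, which the trial could have at no cost, and a clear match between the question and the reported estimate.

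**Working it through.** **Inputs from the article.** Section 2.7 gives a calculation "with an effect size (ES) of 0.61 for the functional outcomes", with alpha "level of 0.05, and a power of 0.80", from which "a total of 68 participants are required" (34 per arm). It continues: "After accounting for a 15% dropout rate, the number of participants in each group is increased to 40". Section 2.8 sets a two-sided p-value "of < 0.05 will be considered statistically significant".

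**Reproducing the plan's figure.** Reading 0.61 as a standardised mean difference d, a one-sided two-sample t test at 0.05 needs 34 per arm (power 0.801), and 34/0.85 = 40. A two-sided test needs 44 per arm; with 34 per arm its power is 0.70. That mismatch is a separate point. Here 34 per arm serves only as a common base.

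**Assumptions not in the article.** Equal SDs; the same correlation ρ between any two visits, taken as 0.3 to 0.8; and a 6-month effect that is sustained (0.61), halved (0.305) or gone (0).

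**Group main effect.** The expected three-visit mean difference is:
- sustained: (0 + 0.61 + 0.61)/3 = 0.41
- halved: (0 + 0.61 + 0.305)/3 = 0.31
- gone: (0 + 0.61 + 0)/3 = 0.20

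So the 8-week effect is reduced by one third, one half or two thirds, whatever ρ is. With variance (1 + 2ρ)/3 for the three-visit mean, power at ρ = 0.5 is 0.53, 0.33 and 0.17.

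**Group × time.** The noncentrality is λ = n Σ(δ_t − mean δ)² / [2(1 − ρ)], on 2 and 2(2n − 2) = 132 df. For a sustained effect the sum of squares is 0.248, so at ρ = 0.5 λ = 34 × 0.248/1 = 8.43 and power is 0.73. An effect that is gone at 6 months gives the same sum of squares. For a halved effect the sum is 0.186, λ = 6.33 and power is 0.60.

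**ANCOVA at 8 weeks.** The effect becomes d/√(1 − ρ²), on 2n − 3 = 65 df. At ρ = 0.5 it is 0.61/0.866 = 0.704; the noncentrality is 0.704 × √17 = 2.90 and power is 0.82. Simulation with 4,000 runs gave 0.80 to 0.81, so the formula is slightly generous.

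| ρ | ANCOVA, 8 weeks, α = 0.05 | Group × time, sustained or gone | Group × time, halved |
|---|---|---|---|
| 0.3 | 0.74 | 0.58 | 0.45 |
| 0.5 | 0.82 | 0.73 | 0.60 |
| 0.7 | 0.93 | 0.92 | 0.83 |
| 0.8 | 0.985 | 0.99 | 0.95 |

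**Fairer comparisons, since the trial asks about two visits.**
- *Alpha split (0.025 per visit).* Power of the 8-week ANCOVA is 0.63, 0.73 and 0.89 at ρ = 0.3, 0.5 and 0.7. With a sustained effect, the interaction equals it at 0.5 and exceeds it at 0.7.
- *Baseline-adjusted mean of the two follow-up visits.* The variance is (1 + ρ)/2 − ρ², which is 0.5 at ρ = 0.5. If the effect is sustained, 0.61/√0.5 = 0.863, the noncentrality is 0.863 × √17 = 3.56 and power is 0.94. If halved, 0.4575/√0.5 = 0.647 and power is 0.75. If gone, 0.305/√0.5 = 0.431 and power is 0.42, below the interaction's 0.73.

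**The case against.** The strongest reply is that this is a conventional, valid analysis, and that the power gap is partly built into the comparison. The article does not make 8 weeks primary, so a single 8-week test at the full 0.05 is a reviewer's choice. This stands: with alpha split over two visits and a sustained effect, there is no per-visit deficit at ρ of 0.5 or more. A gap remains if the effect halves (0.73 against 0.60 at ρ = 0.5), and the adjusted mean of both follow-ups does better when the effect lasts. The size of any loss rests on two quantities that the article does not give.

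Three stronger readings are tempting, and the document does not support them.

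- *The plan's treatment estimate is biased towards zero.* The article never names the group main effect as its treatment estimate. Its stated purpose is to compare trajectories, which points to the interaction. The dilution is a reason not to use the main effect, not evidence that the plan does.
- *The plan gives no estimate at a visit.* It promises post hoc comparisons and between-group differences with CIs. What it does not fix is the visit and the baseline adjustment, and a full analysis plan may do so.
- *Repeated-measures ANOVA does not fit multiple imputation.* It can be run on each completed data set. The narrower point is that Rubin's rules pool an estimate with its standard error directly, whereas F tests and partial eta squared need a separate pooling rule. Leaving that rule to an analysis plan is no fault.

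The one-sided origin of the 68 is a different matter and adds no weight here.

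**Conclusion.** The point holds as an efficiency and clarity recommendation about a valid method. Under equal correlations, 34 per arm and d = 0.61 at 8 weeks, the group × time test falls short of a single 8-week ANCOVA by 16 to 28 percentage points at ρ = 0.3, by 8 to 22 at ρ = 0.5, by 1 to 11 at ρ = 0.7, and by about 0 to 3 at ρ = 0.8 (unrounded powers). The lower end applies to a sustained effect, the upper to a halved one. Part of that difference reflects testing one visit instead of two. Dilution of a three-visit group main effect by at least one third holds at any correlation, provided the 6-month effect is no larger than the 8-week effect. The change deserves making because it is almost free, not because the planned analysis is wrong.

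**What to change.** State the treatment comparison in section 2.8 as a baseline-adjusted between-group difference with 95% CI at 8 weeks and at 6 months. Either of two forms will do:

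- ANCOVA at each visit on group and the baseline value, with the group coefficient pooled over imputations by Rubin's rules; or
- a mixed model for the two follow-up visits with group, visit, group × visit, baseline and baseline × visit, and an unstructured covariance.

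The sponsor should name which visit is primary or adjust for testing two. Say that the group main effect is not the treatment estimate. Partial eta squared may stay as a description, but the adjusted difference should carry the conclusion.

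The cost is a change of wording and syntax and one or two degrees of freedom. No new data are needed. It should be fixed and dated before allocation is unblinded for analysis.
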